#### Secondary outcome measures

The secondary outcome measures include incidences of primary non-function (PNF) defined as the permanent lack of allograft function from the time of transplantation (This will include graft losses due to irreversible rejection and vascular thrombosis. The cause of graft loss will be recorded.); the duration of DGF in days; functional DGF (fDGF) defined as <10% fall in serum creatinine for 3 consecutive days in the first week post-transplant; creatinine reduction ratio day 2 (CRR2=creatinine day 1−creatinine day 2/creatinine day 1) and CRR5 (CRR5=pretransplant creatinine−creatinine day 5/pretransplant creatinine);^19^ length of hospital stay, rates of biopsy-proven acute rejection rate and measures of renal function (serum creatinine and estimated glomerular filtration rate (eGFR)) at 1, 3, 6 and 12 months post-transplant. Patient survival (time from transplant to death) and allograft survival (time from transplant to graft loss or return to dialysis) will be recorded. The EVNP score will be calculated for each kidney undergoing EVNP (table 1). The predictive value of this assessment score on graft function and outcome will be evaluated. A clinical decision on the suitability of the kidney for transplantation will be made using normal criteria prior to perfusion. However, the EVNP assessment score will be taken into consideration. Arterial and venous samples will be collected during perfusion and used to measure oxygen consumption, acid–base balance and concentrations of sodium, potassium, glucose, lactate and calcium. Concentrations of sodium and potassium will also be measured in the urine at the end of EVNP.

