#### Analysis population and principles

The population used for efficacy analyses will be an intent-to-treat population including all eligible randomised patients. This will be the primary analysis for the trial. Characteristics of all randomised patients will be tabulated by arm of the trial to describe the cohort.

The primary and secondary outcomes will also be analysed per protocol.

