#### Secondary outcomes

*PNF*: The number of patients experiencing PNF in each arm will be compared using Fisher's exact text. The cause of graft loss will be tabulated by arm. The duration of DGF in days will be summarised using the Kaplan-Meier estimate of the duration of DGF for all those who experienced DGF and compared using a log-rank test.

*Outcome measures*: The number of patients that experience functional DGF will be compared using Fisher's exact test. The CRR2 and CRR5 will be compared by arm using a two-sample t-test. The length of hospital stay, defined from admission to discharge, will be estimated using the Kaplan-Meier method, with deaths in hospital censored, and compared between arms using the log-rank test.

*Biopsy-proven acute rejection rate*: The number of patients in each arm will be compared using Fisher's exact test. Longitudinal changes in serum creatinine and eGFR will be separately assessed at 1, 3, 6 and 12 months post-transplant and mean values compared using two-way analysis of variance with repeated measures for patients in each arm of the trial. Any difference between arms in the way serum creatinine and eGFR change over time will also be assessed using this model. Patient survival (time from transplant to death) and allograft survival (time from transplant to graft loss or return to dialysis) will be analysed using a Kaplan-Meier estimate of the probability of an event after 12 months and a log-rank test. Time to graft loss or return to dialysis will be modelled.

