### Analysis population and missing data

Normally if a patient experiences DGF, they would remain in hospital for a minimum of 7 days. Hence, for pragmatic reasons, if a patient is discharged from the hospital prior to 7 days post-transplant and the patient is known to be alive at 7 days post-transplant, then such patients will be imputed to have not experienced DGF. Some patients may also withdraw consent, be withdrawn or die during the conduct of the trial. In any of these cases, it is impossible to know whether such patients are either less or more likely to experience DGF had they not experienced early censoring. Sensitivity analyses will be performed to account for this.

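### Repeated-measures ANOVA for creatinine and eGFR, in its classical form, drops patients with any missing visit and departs from intention to treat; a mixed model with a stated rule for graft failure and death fits better

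*Protocol article*

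**What the plan says.** The Secondary outcomes part of the analysis section sets the visits: "Longitudinal changes in serum creatinine and eGFR will be separately assessed at 1, 3, 6 and 12 months post-transplant". It names the method, "mean values compared using two-way analysis of variance with repeated measures for patients in each arm of the trial", and uses it for the arm-by-time question too: "Any difference between arms in the way serum creatinine and eGFR change over time will also be assessed using this model".

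Analysis population and principles defines the efficacy population as an "intent-to-treat population including all eligible randomised patients".

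Analysis population and missing data foresees incomplete follow-up: "Some patients may also withdraw consent, be withdrawn or die during the conduct of the trial". Its only imputation rule concerns patients discharged before day 7 and known to be alive at day 7: "then such patients will be imputed to have not experienced DGF". The sensitivity analyses it announces are also framed around delayed graft function (DGF).

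Graft loss is expected and has its own analyses. Of primary non-function (PNF) the outcome section says: "This will include graft losses due to irreversible rejection and vascular thrombosis". The secondary analyses include "allograft survival (time from transplant to graft loss or return to dialysis"), by Kaplan-Meier and log-rank test.

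**The concern.** Two things do not fit together. The population is all eligible randomised patients, but classical two-way repeated-measures ANOVA needs a full set of four values per patient. Someone seen at months 1, 3 and 6 but not at month 12 contributes nothing. The method also assumes sphericity, meaning that differences between any two visits have equal variance. That is hard to expect with visits at 1, 3, 6 and 12 months, because neighbouring visits usually correlate more strongly than distant ones. The assumption affects the tests of time and of arm by time, and the article wants the latter from this model.

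Graft failure and death raise a separate question. EVNP may change graft loss, so any rule that removes failed grafts conditions on an event after randomisation. The article names no other between-arm analysis of longer-term graft function, so its means will be read as a comparison of the randomised arms. At stake are precision and, under some ways of handling failed grafts, the direction of a modest difference.

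**Working it through.** The article states no figure for the creatinine or eGFR analysis, so there is none to reproduce. Its only attrition figure is the 6% withdrawal allowance under Sample size determination, which is consistent with its totals: 376 / 0.94 = 400.

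**1. Share of patients with all four visits**

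Input from the article: four visits and 200 patients per arm. Assumed: a proportion m of patients misses each visit, independently across visits.

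Complete share = (1 − m)^4.

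- m = 2%: 0.98^4 = 0.922, about 184 of 200 per arm
- m = 5%: 0.95^4 = 0.815, about 163 of 200
- m = 10%: 0.90^4 = 0.656, about 131 of 200

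If the 6% withdrawals were the only source of missing values, the complete share would be about 94%, or 0.94 × 200 = 188 per arm. Isolated missed visits, deaths and graft failures would lower it.

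**2. Possible shift from leaving out failed grafts**

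All inputs here are assumptions: latent eGFR with mean 45 and SD 16 mL/min in both arms (no true difference), graft loss of 10% against 5% or 15% against 5%, and a correlation r of 0.3 to 0.9 between function and a normally distributed tendency to graft survival. The lowest share l on that tendency loses the graft.

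Mean among retained grafts = 45 + 16 × r × k(l), where k(l) = φ(z_l) / (1 − l), with φ the standard normal density and z_l the l-quantile. This gives k(0.05) = 0.109, k(0.10) = 0.195 and k(0.15) = 0.274.

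Difference, arm with more losses minus the other:

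- 10% against 5%: 16 × r × (0.195 − 0.109) = 1.38r, so 0.4 at r = 0.3, 0.8 at r = 0.6 and 1.2 at r = 0.9
- 15% against 5%: 16 × r × (0.274 − 0.109) = 2.65r, so 0.8, 1.6 and 2.4
- r = 0 (loss unrelated to function): 0 in both cases

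Simulation with the same inputs gave 0.45, 0.89 and 1.31 for the first case and 0.82, 1.64 and 2.38 for the second. These agree with the formula apart from simulation error.

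**3. The same data with failed grafts kept at eGFR 10 (assumed)**

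Mean = (1 − l) × retained mean + l × 10.

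- 10% against 5%: difference = −1.75 + 1.16r, so −1.4, −1.1 and −0.7 at r = 0.3, 0.6 and 0.9
- 15% against 5%: difference = −3.50 + 2.08r, so −2.9, −2.3 and −1.6

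The sign reverses. The value at r = 0, (0.10 − 0.05) × (45 − 10) = 1.75 mL/min, is the effect of scoring failed grafts at 10. It does not measure the bias from leaving them out.

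**4. Scale**

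With SD 16 and 200 per arm, the standard error of a difference in means is 16 × √(2/200) = 1.6 mL/min. The shift in step 2 is below one standard error for 10% against 5%, and up to about 1.5 standard errors (2.4 / 1.6) for 15% against 5%.

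**The case against.** The article says that its analysis section is a summary and that a full statistical analysis plan will follow. How missed visits, deaths, failed grafts and non-sphericity are treated commonly belongs there, so their absence here is not an error. Naming ANOVA does not by itself prescribe deletion of incomplete patients. This stands as far as missing detail goes. It does not cover the named method, which the article fixes and which in its ordinary form conflicts with the stated population.

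A reader might infer that failed grafts are left out and that the arm losing more grafts will therefore look better. The documents do not support this. They give no such rule, and a patient back on dialysis can still have a creatinine value, which would count against that arm. The shift is zero if loss is unrelated to function and reverses if failed grafts enter with poor values. A difference in losses would also not be hidden: PNF is compared by arm with causes of loss tabulated, and patient and allograft survival have their own tests.

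The numbers are also open to challenge. The article gives only 6% withdrawal overall. Per-visit missingness, graft-loss rates and the eGFR distribution are all assumed, and the resulting shift is small beside the standard error except under the stronger assumptions. That stands, and the figures should be read as illustrations.

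**Conclusion.** The point holds for the choice of method. Two-way repeated-measures ANOVA in its classical form is a complete-case analysis with a sphericity assumption. It fits poorly with an intention-to-treat population and with the withdrawals, deaths and graft losses that the article foresees, and the only missing-data rule given concerns DGF. On assumed independent missingness of 2% to 10% per visit, 8% to 34% of patients would fall out of the analysis, although most would have usable values.

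The graft-loss part holds only as a conditional risk: if failed grafts drop out and loss is related to poor function, the comparison can favour the arm with more losses. On the assumed inputs this is about 0.4 to 1.2 mL/min for 10% against 5% loss, and 0.8 to 2.4 mL/min for 15% against 5%. Handling that is still unstated could therefore decide the direction of a small difference.

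This is a secondary outcome. The primary DGF analysis and the sample size are unaffected. The change is worth making because it improves a stated choice at little cost.

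**What to change.** Replace the ANOVA with a linear mixed model for repeated measures on all available visits. Include arm, visit and arm by visit, with an unstructured covariance across the four visits. Adjust for donor age, which the primary model already uses, and allow for paired kidneys from one donor. This uses partial data and does not need sphericity. It relies on missed visits being missing at random given the observed values.

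A mixed model alone does not resolve graft loss or death, since it would implicitly extrapolate function for a graft that has failed. Add a supplementary pre-specified analysis that keeps failed grafts at a fixed low eGFR or at the worst rank, and state the rule for patients who die. State also, for the main model, whether creatinine and eGFR values after a return to dialysis are used.

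The cost is a few sentences in the analysis plan, standard software and slightly more analysis work, with no extra data. The article already requires the full plan before the first interim analysis, which is the natural point to make the change.

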### Analysis population and missing data

Normally if a patient experiences DGF, they would remain in hospital for a minimum of 7 days. Hence, for pragmatic reasons, if a patient is discharged from the hospital prior to 7 days post-transplant and the patient is known to be alive at 7 days post-transplant, then such patients will be imputed to have not experienced DGF. Some patients may also withdraw consent, be withdrawn or die during the conduct of the trial. In any of these cases, it is impossible to know whether such patients are either less or more likely to experience DGF had they not experienced early censoring. Sensitivity analyses will be performed to account for this.

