### Randomisation

Patients will be allocated at random in a 1:1 ratio to either static cold storage (CS) plus 1 hour of EVNP (n=200) or CS (n=200) only. A patient information sheet will be given to potential recruits on admission for DCD kidney transplantation and written informed consent will then be obtained (see online supplementary appendices 1 and 2). Randomisation will be performed after the transplant recipient and kidney have both arrived in the transplanting centre and a final decision to proceed with transplantation has been made by a member of the study team. The randomisation will be performed on a web-based system (sealed envelope) which uses a computer-generated randomisation sequence. In cases where paired kidneys from the same donor are transplanted in the same centre, one kidney from the pair will be randomly allocated to CS and the other to EVNP. In these cases, the randomisation will also determine which kidney (right or left) will be transplanted first. Owing to the nature of the trial, no one is blinded to treatment allocation.

10.1136/bmjopen-2016-012237.supp1supplementary appendix

10.1136/bmjopen-2016-012237.supp2supplementary appendix

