### Outcomes

#### Primary outcome measure

The primary outcome measure is DGF defined as the need for dialysis in the first 7 days post-transplantation.^18^

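### The early-discharge imputation rule for the primary outcome has no condition on dialysis, so it can code patients who meet the DGF definition as not having DGF

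*Protocol article*

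**What the plan says.** Under Primary outcome measure the article states: "The primary outcome measure is DGF defined as the need for dialysis in the first 7 days post-transplantation". That wording is not limited to dialysis given in hospital.

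A second rule that decides who counts as a case stands under the heading "Analysis population and missing data". It applies "if a patient is discharged from the hospital prior to 7 days post-transplant and the patient is known to be alive at 7 days post-transplant", and its result is that "such patients will be imputed to have not experienced DGF". The reason given is pragmatic: "Normally if a patient experiences DGF, they would remain in hospital for a minimum of 7 days".

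The same paragraph then turns to patients who withdraw, are withdrawn or die, says that their DGF status cannot be known, and closes: "Sensitivity analyses will be performed to account for this". The Randomisation section records that "no one is blinded to treatment allocation".

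**The concern.** The rule has two triggers, early discharge and being alive at day 7, and neither concerns dialysis. Discharge serves as a proxy for the outcome. The proxy is justified by what normally happens, and that word allows for exceptions. Two kinds of patient fall into the gap: one dialysed soon after surgery who goes home on, say, day 6, and one who goes home early and is dialysed as an outpatient before day 7. Both meet the primary definition, and the rule as worded codes both as not having DGF.

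This is the primary endpoint. If the error is equally common among DGF cases in both arms, it shrinks the absolute difference and costs power. If early discharge of DGF patients is more common in one arm, it moves the estimated effect in that arm's favour. Staff who decide on discharge know the allocation, and length of stay is itself a secondary outcome compared between arms, so the trial allows that discharge timing may differ. Recoded patients would also leave the analysis of DGF duration, which is confined to those who experienced DGF.

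**Working it through.** **The two rules side by side**

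| Patient, alive at day 7 | Primary definition | Imputation rule, literal | Imputation rule, unobserved status only |
|---|---|---|---|
| Dialysed in hospital, discharged before day 7 | DGF | no DGF | DGF (recorded dialysis stands) |
| Discharged early, outpatient dialysis by day 7, not ascertained | DGF | no DGF | no DGF |
| Discharged early, no dialysis to day 7 | no DGF | no DGF | no DGF |

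The two readings of the rule differ on the first row, and both conflict with the definition on the second.

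**Inputs from the Sample size determination section.** DGF 50% v 35%, power 80%, α = 0.05 (taken as two-sided, which the article does not state), 376 evaluable patients and 400 recruited after 6% withdrawal. With 1:1 allocation, 376/2 = 188 per arm.

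**The plan's own figure.** The two-sided two-proportion formula with pooled variance gives 170 per arm (340 in total). With continuity correction it gives 183 per arm (366), within 3% of 376. 376/0.94 = 400. The stated size is therefore reproduced closely, and the present point does not depend on the difference.

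**Size of the effect.** The documents do not say what share m of DGF patients leave hospital alive before day 7 and would be recoded, so m is an assumption throughout. Observed rate = true rate × (1 − m).

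Power = Φ[(d − 1.96·s0)/s1], where d is the observed difference, s0 = √(2·p̄(1 − p̄)/188), p̄ is the mean of the two rates, and s1 = √((p0(1 − p0) + p1(1 − p1))/188). There is no continuity, covariate or interim adjustment.

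For m = 0: d = 0.15, s0 = 0.0510, s1 = 0.0504; (0.15 − 1.96 × 0.0510)/0.0504 ≈ 0.99, power 0.840.

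Equal recoding in both arms:

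| m | CS v EVNP, observed | Difference | Power |
|---|---|---|---|
| 0 | 50.0% v 35.0% | 15.0 points | 0.840 |
| 2% | 49.0% v 34.3% | 14.7 | 0.827 |
| 5% | 47.5% v 33.25% | 14.25 | 0.806 |
| 10% | 45.0% v 31.5% | 13.5 | 0.770 |
| 20% | 40.0% v 28.0% | 12.0 | 0.691 |

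The relative risk stays at 0.70 in every row. In patients, m = 5% means 188 × 0.50 × 0.05 = 4.7 recoded in the CS arm and 188 × 0.35 × 0.05 = 3.3 in the EVNP arm.

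Unequal recoding with no true effect (50% in both arms), chance of a significant result favouring EVNP, nominally 2.5%:

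- 5% CS v 15% EVNP: 0.50 × 0.95 = 47.5% v 0.50 × 0.85 = 42.5%, a spurious 5-point difference; s0 = 0.0513, s1 = 0.0512; (0.05 − 1.96 × 0.0513)/0.0512 ≈ −0.99, probability about 0.16.
- 5% CS v 10% EVNP: 47.5% v 45.0%, a spurious 2.5-point difference, probability about 0.07.

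**The case against.** A reader might infer that the plan sets out to overwrite dialysis that was actually recorded. The article does not say so, and the context points the other way. The rule stands under a missing-data heading, it speaks of imputing, and the next sentence adds withdrawal and death with the word also, which places early discharge among the ways that follow-up to day 7 becomes incomplete. Duration of DGF is a secondary outcome, so dialysis has to be recorded in any case. On that reading, a patient dialysed in hospital has an observed outcome and nothing is imputed. This stands as a plausible account of the intention, but the rule does not state the restriction, and the reading does not reach unascertained outpatient dialysis after discharge.

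A reader might also infer serious bias or a serious loss of power. The documents support neither. Their only statement on frequency is that DGF patients normally stay at least 7 days, which points to a small share, and at 2% or 5% the loss is about 1 to 3 percentage points. Open-label allocation makes a difference in discharge between arms possible, but nothing in the article shows that one is expected.

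The closing promise of sensitivity analyses could be stretched to cover early discharge, but the sentence before it concerns withdrawal and death. The article leaves detail to a full analysis plan, which could clarify the rule. The rule is stated here, however, not left open, and a plan that repeated it would carry the gap forward.

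**Conclusion.** The point holds as a defect of wording in the rule that decides the primary outcome. As written, it contradicts the definition of DGF for patients dialysed before an early discharge. Even read narrowly, it codes unascertained outpatient dialysis up to day 7 as no DGF. It does not show that recorded dialysis will be replaced.

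The size cannot be fixed from the documents. It runs from about 1 percentage point of power if 2% of DGF cases are recoded equally to about 15 points if 20% are. The false-positive risk in favour of EVNP arises only if recoding is more common in the EVNP arm, which is an assumption. The effect is probably small if the stated rationale holds. The rule deserves correction because it touches the primary endpoint of an unblinded trial and costs little to put right.

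**What to change.** Reword the rule in the protocol and carry it into the analysis plan before the first interim analysis:

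- Any dialysis recorded from transplant to day 7, inpatient or outpatient, counts as DGF whatever the discharge date.
- For patients discharged early, dialysis status to day 7 is obtained at the same time as vital status at day 7, which the rule already requires to be known.
- No DGF is imputed only when no dialysis was recorded before discharge and status to day 7 cannot be obtained.
- The patients imputed in this way are counted by arm and included in the sensitivity analyses, for example by recoding them as DGF.

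The cost is a short change of text and one added data check for patients discharged early. The design, sample size and main analysis model stay as they are.

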### Safety outcomes

Incidences of acute rejection, renal artery or renal vein thrombosis, complications of the renal transplant biopsy and the number of hospital admissions for any recognised complication of renal transplantation and immunosuppression will be summarised by arm.

The University of Cambridge and Cambridge University Hospital National Health Service (NHS) Foundation Trust will be the sponsor for this study. A Trial Steering Committee will meet six monthly to review the trial, monitor recruitment rates to consider protocol amendments and provide advice. A Trial Management Group will be responsible for the Ethics Committee application and the production of reports and the day-to-day running of the trial. A Data Monitoring Committee will consist of three independent members with expertise in renal transplantation, clinical trials and statistics. They will meet at least annually to review data, primarily concentrating on patient safety.

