## Introduction

Kidney transplantation continues to be limited by a shortage of organ donors. In response to this, there has been an increase in the use of kidneys from marginal donors and a significant proportion of transplant kidneys are now provided by donation after circulatory death (DCD) donors.^1^ DCD kidneys inevitably sustain a warm ischaemic insult prior to retrieval and 50–60% of these kidneys have delayed graft function (DGF) after transplantation.^1^ DGF is associated with an increased risk of acute rejection, longer in-patient stay and therefore greater cost, and may also reduce allograft survival.^1–7^ Moreover, when compared with standard criteria donors, DCD kidneys are three times more likely to be declined for transplantation due to concerns over their quality.^8^
^9^

Organ preservation has traditionally relied on hypothermic techniques based on the principle that refrigeration reduces cellular metabolism and tissue oxygen requirements. The problem is that in the anoxic hypothermic environment anaerobic cellular respiration continues, albeit at a slow pace. Oxidative phosphorylation is uncoupled and mitochondrial ATP production by chemiosmosis ceases.^10^ ATP continues to be generated at a much slower rate by substrate-based phosphorylation in the glycolytic pathway. This leads to depletion of intracellular ATP stores. Anaerobic respiration generates lactic acid leading to worsening intracellular acidosis and eventually loss of cell viability.^10^ The initial warm ischaemic injury sustained by DCD kidneys makes them less tolerant of cold ischaemic injury during hypothermic preservation.^11^
^12^

Normothermic perfusion techniques offer an alternative form of organ preservation and resuscitation that has the potential to limit some of the effects of hypothermic preservation techniques.^13^ Ex vivo normothermic perfusion (EVNP) is a novel technique that may help to recondition ischaemically injured kidneys prior to transplantation.^13^ The aim of EVNP is to restore metabolism and function to the kidney prior to transplantation by circulating a warm oxygenated red cell-based solution through the kidney.

EVNP has recently been introduced into clinical practice for kidneys from marginal donors.^13–17^ The early experience of renal transplantation after EVNP shows that the technique is feasible, safe and may improve early graft function.

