### Postperfusion

After EVNP, kidneys will be flushed with ∼500 mL of cold (4^°^C) HOC (Baxter Healthcare, UK) to remove the perfusate and then placed back in ice until transplanted. Prior to transplantation, the arterial Carrel patch may have to be excised along with a short segment of vein in order to remove the cannula ligature sites.

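### Complications outside the named types are summarised only as hospital admissions, so those arising during the transplant stay are left out of the by-arm safety summary

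*Protocol article*

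**What the plan says.** The Safety outcomes section of the protocol article uses two units. The first is incidence, with no condition on where the patient is at the time: "Incidences of acute rejection, renal artery or renal vein thrombosis, complications of the renal transplant biopsy". The second covers every other complication and is a count of admissions: "the number of hospital admissions for any recognised complication of renal transplantation and immunosuppression will be summarised by arm".

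Two other statements bear on how the admissions count behaves. The analysis of secondary outcomes treats the transplant stay as one episode: "The length of hospital stay, defined from admission to discharge". The Introduction and the missing-data section link the primary outcome to the length of that episode: "DGF is associated with an increased risk of acute rejection, longer in-patient stay and therefore greater cost", and "Normally if a patient experiences DGF, they would remain in hospital for a minimum of 7 days".

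EVNP is given once, for 60 minutes, before implantation. The Postperfusion section notes that afterwards "the arterial Carrel patch may have to be excised along with a short segment of vein".

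**The concern.** An admission is a poor unit for early surgical harm. The patient is already in hospital, so a complication in the first days after surgery causes no new admission. If the section is followed as written, such an event enters the safety summary only when it is one of the named types.

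This matters more than usual here because the intervention acts once, immediately before surgery, and involves cannulation and sometimes trimming of the vessels. Harm from handling the kidney could plausibly appear before first discharge.

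There is a second, conditional problem. Whether a complication is counted depends on whether the patient has gone home, and the protocol says that DGF delays going home. If EVNP reduces DGF as planned, the two arms have different counting windows, and the safety count is no longer independent of the efficacy result.

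**Working it through.** **1. What the text counts during the transplant stay**

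| Event during the transplant stay | Reported by arm? | Section |
|---|---|---|
| Acute rejection, renal artery or vein thrombosis, biopsy complication | Yes, as incidence | Safety outcomes |
| Graft that never works, including thrombosis or irreversible rejection | Yes, as primary non-function | Secondary outcome measures; Secondary outcomes |
| Graft loss and its cause; death | Yes, from transplant | Secondary outcomes |
| Bleeding, urine leak, infection or vessel repair, with patient and graft surviving | No; at most an indirect trace in length of stay | none |

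The last row is the gap. It follows from the wording and needs no assumption about rates.

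**2. How far the admissions count could depend on DGF**

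The plan gives no safety figure to reproduce. The only figures taken from it are the DGF rates under Sample size determination, 50% with cold storage (CS) and 35% with EVNP. As a check on those rates, a two-sided 5% test with 80% power and continuity correction needs 2 × 183 = 366 patients, against the stated 376 (2.7% apart); 376/0.94 = 400. Nothing below depends on the total.

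Assumed, because the document does not give them:
- length of stay d0 without DGF and d1 with DGF;
- S(t), the share of complications arising after day t;
- r, the complication rate with DGF relative to without;
- every complication after discharge leads to one admission.

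For an arm with DGF rate p:
- counted: C(p) = p·r·S(d1) + (1 − p)·S(d0)
- true: T(p) = p·r + (1 − p)
- counted ratio, EVNP to CS: C(0.35)/C(0.50)
- true ratio: T(0.35)/T(0.50)
- share missed in an arm: 1 − C/T

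Worked example with stays of 7 and 14 days, exponential onset with mean 14 days, and r = 1:
- S(7) = exp(−0.5) = 0.607 and S(14) = exp(−1) = 0.368
- EVNP: 0.35 × 0.368 + 0.65 × 0.607 = 0.523
- CS: 0.50 × 0.368 + 0.50 × 0.607 = 0.487
- ratio: 0.523/0.487 = 1.073, when the true ratio is 1
- missed: 48% in EVNP and 51% in CS

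Other cases with r = 1:

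| Stay without / with DGF (days) | Timing of complications | Missed, EVNP / CS | Counted ratio |
|---|---|---|---|
| 5 / 10 | even over 365 days | 2% / 2% | 1.002 |
| 5 / 10 | even over 30 days | 22% / 25% | 1.033 |
| 5 / 10 | exponential, mean 14 days | 37% / 41% | 1.053 |
| 7 / 14 | even over 365 days | 3% / 3% | 1.003 |
| 7 / 14 | even over 30 days | 31% / 35% | 1.054 |
| 7 / 21 | even over 365 days | 3% / 4% | 1.006 |
| 7 / 21 | even over 30 days | 40% / 47% | 1.131 |
| 7 / 21 | exponential, mean 14 days | 53% / 59% | 1.139 |

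**3. If DGF itself brings more complications**

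- r = 1.2: true ratio = 1.07/1.10 = 0.973
- r = 1.5: true ratio = 1.175/1.25 = 0.940

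Over the same stays and timings, the counted ratio then runs from 0.942 (5/10 days, even over 365 days, r = 1.5) to 1.116 (7/21 days, exponential with mean 14 days, r = 1.2). Relative to the truth, the count is still shifted against EVNP, by at most 1.087/0.940 = 1.156. The raw count can nonetheless favour EVNP.

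**4. With the count started at transplant**, S is replaced by 1 in both arms. C then equals T, and the shift disappears whatever the stays or timing.

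**The case against.** A journal article condenses the full protocol. One sentence on what will be summarised does not show that nothing else is recorded, and case report forms and adverse-event procedures are commonly left to documents not shown. This stands against a stronger reading, that the trial fails to collect in-stay complications or ought to list perfusion events such as circuit failure. The article does not show that. It does not remove the point, because the article states the by-arm measure and the unit it chose leaves these events out.

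A reader might also infer that the safety comparison misses EVNP's main risk window. The documents do not support that. Thrombosis, the obvious serious consequence of handling the vessels, is counted whenever it occurs. Of primary non-function the article says: "This will include graft losses due to irreversible rejection and vascular thrombosis". Cause of graft loss, graft survival and patient survival are reported by arm, length of stay is compared, and a Data Monitoring Committee reviews safety. That EVNP harm would fall mostly among the uncounted complications is inference.

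A third inference is that the count is tilted against EVNP and will make it look less safe. The direction follows only if EVNP lowers DGF. The size rests on assumed stays and timing, and the Introduction's own link between DGF and rejection allows DGF patients to have more complications, in which case EVNP may show fewer admissions. The effect is also small beside chance. Assuming, for illustration, 60 complications in each arm, the largest equal-rate case counts 0.472 × 60 = 28.3 against 0.415 × 60 = 24.9. That difference is about 3.5, with a Poisson standard error of √(28.3 + 24.9) = 7.3. The summary is descriptive, and no test or decision rule is attached to it.

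**Conclusion.** The point holds in a limited form. As worded, the safety summary leaves out unlisted complications that arise during the transplant stay and cost neither life nor graft. That is a poorly chosen unit in the stated text and rests on no assumption. How many events are lost is unknown: about 2% to 4% if complications are spread evenly over a year, and about 37% to 59% if they cluster in the first weeks, under the assumed stays.

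Dependence on the primary outcome is possible but not established. If EVNP achieves 35% DGF against 50%, the distortion relative to the truth ranges from negligible to about 15% (1.002 to 1.14 at equal rates, 1.156 at most with DGF patients at 1.5 times the rate). It should be described as a risk of the chosen unit and not as a known bias. The fix deserves making because it is cheap and settles both parts.

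**What to change.** In Safety outcomes, replace the admissions count with two figures by arm: the number of patients with any recognised complication of transplantation or immunosuppression, and the number of such complications. Count both from transplant to 12 months and state that the transplant admission is included. Keep readmissions for complications as a separate line, since they are informative about burden. Leave the incidences of rejection, thrombosis and biopsy complications as they are.

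The cost is some extra data entry at the four centres, to the extent that the case report forms do not already hold these events, and one more table. No patients, visits or procedures are added.
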